### Patient eligibility

To be eligible for the trial, patients must meet the following inclusion criteria at randomisation: (1) Diagnosis of prediabetes or type 2 diabetes according to the Czech guidelines for GPs [59, 60], i.e. fasting plasma glucose 5.6–6.9 mmol/l, or 2-h plasma glucose of 7.8–11.0 mmol/l after ingestion of 75 g of oral glucose load for the diagnosis of prediabetes, and fasting plasma glucose ≥ 7.0 mmol/l, or 2-h plasma glucose ≥ 11.1 mmol/l after ingestion of 75 g of the oral glucose load for the diagnosis of type 2 diabetes. (2) Age 18 years or older. (3) Followed for prediabetes/diabetes by a participating GP. Of note, in the Czech Republic, only uncomplicated type 2 diabetes patients with glycated haemoglobin HbA_1c_ ≤ 53 mmol/mol and not taking insulin are commonly followed by a GP; other type 2 diabetes patients are usually followed by a specialist-diabetologist. (4) Regular users of a mobile phone (not necessarily a smartphone), able and willing to answer calls and read text messages as part of the study. (5) Able and willing to wear and use a wrist-worn Fitbit activity tracker for the study duration. (6) Written informed consent provided before any assessment related to the study.

Patients are excluded from the trial if they are: (1) Unable to walk for any reason. (2) Pregnant. (3) Having a household member already recruited for this study to avoid contamination. (4) Living in a residential or nursing care home where the imposed regime could interfere with the intervention. (5) Having any co-morbid conditions that would seriously affect their adherence to the trial procedures (e.g., active malignancy; recent (< 3 months) myocardial infarction, coronary artery bypass graft or cerebrovascular accident; renal disease requiring dialysis; neurological condition (e.g., Parkinson disease); cognitive impairment, or significant hearing or visual impairment; hip or knee joint replacement within three months; major surgery planned within the next 12 months).

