#### Phone contact by the research team member

The patients will be made aware of their allocation by a research team member via a phone call. During this call, the research team member will also check if the patient has successfully initiated the Fitbit (by asking the patient) and is regularly syncing it with their account (by checking the account directly). Patients who experience trouble with the initialisation or syncing will be provided with basic technical support during the call to ensure that as many patients as possible continuously sync their Fitbit data for analytical purposes.

The research team member will check monthly if the patients continue syncing their Fitbits; if they do not, they will be contacted by phone and reminded to do so. The patients unable to sync their Fitbits despite the support and those without their own smartphone will be asked to self-monitor by keeping a paper-based diary with daily records of their step count as measured by Fitbit.

To prevent interference of push notifications built into the Fitbit app (e.g., reminders to move, notifications of step goal milestones) with our study, all these notifications will be remotely switched off by the research team member. In addition, the research team member will instruct the patients not to change the settings of their Fitbit app.

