**Fig. 2 Fig2:**
[figure not shown]
Scheme of the HealthReact system. The HealthReact system triggers sending out just-in-time text messages based on data recorded by the Fitbit tracker

For the mHealth intervention to function optimally, patients must be equipped with a smartphone able to run the Fitbit app (Android 8.0 or iOS 14.0 and later as of January 2023) with a continuous internet connection. Patients who fall short of such requirements will receive adapted mHealth intervention that is equalised for the total number of text messages and the behaviour change techniques used. For example, in patients without a mobile data plan who only sync their mobile when connected to wifi, the prompts to increase their walking pace could not be triggered just in time when they walk, but would still be sent out at a pre-specified fixed time. In patients that do not sync reliably even when at home, the prompts to interrupt sitting could not be triggered just in time and would be replaced with a general reminder to regularly interrupt sitting. Finally, in patients without a smartphone or unable to sync any Fitbit data to HealthReact for other reasons, messages reviewing their step goal and providing feedback could not be personalised, but would still be sent out as simple reminders to review the set goal and provide encouragement.

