#### Statistical analysis

The primary outcome (change in daily step count at six months) will be analysed using a linear mixed-effect model accounting for clustering at the GP level (random effect) and adjusted for baseline value, prediabetes/diabetes condition, and sex (fixed effects) [91]. The intervention effect (adjusted value for change in intervention minus change in control) will be reported as the mean (95% CI) and associated *p*-value (considered significant at p < 0.05). The intervention effect for secondary outcomes (Table 1) will be assessed using the same approach and reported as a mean (95% CI). However, individual *p*-values will not be reported for secondary outcomes as the adjustment for multiple testing will not be undertaken, and outcomes will be interpreted with caution in relation to the overall pattern of results. Assumptions of normality will be tested, and an alternative distribution will be used where necessary. Baseline characteristics will be compared between the intervention and control arms. If meaningful differences are demonstrated, the measure will be added to statistical models as a covariate. The analyses of the outcomes will be undertaken using both the intention-to-treat principle, considering all patients as randomised regardless of protocol adherence, and a per-protocol analysis, including only patients (a) syncing their Fitbit trackers at least once a month (both arms), (b) engaging in at least five phone counselling sessions, and (c) receiving text messages for the entire study duration (intervention arm only). The impact of missing data will be assessed using a sensitivity analysis, and missing data will be imputed using multiple imputations created by predictive models based on the patients with complete data [92]. All statistical analyses will be performed using an R environment for statistical computing.

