Secondly, also in line with the pragmatic trial design, we attempted to make the eligibility criteria as wide as possible. Thus, even though achieving the full potential of the intervention requires a smartphone with a mobile data plan, we allow for the inclusion of patients that only have a basic cell phone able to receive calls and text messages. These patients will receive an adapted version of the mHealth intervention, lacking the just-in-time messages, but equalised in terms of the number and types of messages. Consequently, the trial will enable the recruitment of older and lower socioeconomic status patients, thus increasing its external validity.

Thirdly, the recruitment process is designed to minimise previously described self-selection and selection biases [29, 63, 97, 98]. The self-selection bias commonly occurs when potentially eligible patients identified in GPs databases are recruited systematically, e.g., via mail invites. Usually, only a small fraction of patients answer these invites, and these patients are not representative of the target population: they are typically younger, more likely to be female, better educated and more physically active [97–99]. The self-selection bias can be reduced using opportunistic recruitment when GPs address patients coming to regular visits and invite them personally to participate [64]. However, this approach leads to selection bias, when GPs preferentially pick patients they believe benefit most from the intervention [29, 63]. In the ENERGISED trial, we apply opportunistic recruitment but try to minimise the selection bias by implementing the following procedures: (A) For each practice, we first compile a list of all potentially eligible patients and randomly select a limited sample available for recruitment. (B) We then ask GPs to address all patients from this sample, evaluate their eligibility, invite those who are eligible, and record eventual reasons for exclusion or patients' refusal to participate. (C) Only after a GP addresses all patients from the sample, we provide them with a new random sample until the recruitment is finished. The process is described in more detail in the Methods section. While this approach cannot completely eliminate the self-selection and selection biases, it will enable us to explore the potential extent and direction of the bias by providing a clear denominator and evaluate the feasibility of the intervention for translation into routine care.

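### The per-protocol rule excludes patients who follow the no-smartphone pathway, and two of its three criteria filter only the intervention arm

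*Protocol article*

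**What the plan says.** The Statistical analysis section sets two analyses side by side: "The analyses of the outcomes will be undertaken using both the intention-to-treat principle" and "a per-protocol analysis, including only patients (a) syncing their Fitbit trackers at least once a month (both arms"). This first per-protocol criterion covers both arms. The others read "b) engaging in at least five phone counselling sessions, and (c) receiving text messages for the entire study duration (intervention arm only"). The restriction to the intervention arm must cover the counselling criterion too, because Table 2 gives counselling and text messages to that arm only.

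Elsewhere the article provides for patients who cannot sync:

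- Patient eligibility admits "Regular users of a mobile phone (not necessarily a smartphone").
- The section on phone contact by the research team says that "those without their own smartphone will be asked to self-monitor by keeping a paper-based diary with daily records of their step count". The same instruction covers patients who cannot sync despite support.
- The mHealth intervention section describes adapted messages "in patients without a smartphone or unable to sync any Fitbit data to HealthReact for other reasons", equalised for number of messages and behaviour change techniques.
- The Discussion presents this as a strength: "we allow for the inclusion of patients that only have a basic cell phone able to receive calls and text messages".

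**The concern.** A per-protocol set should hold the patients who did what the protocol asked of them. Here a patient on the diary pathway can keep the diary, take all seven calls and receive messages for 12 months, and still be excluded for not syncing. The result would then not describe the older and less advantaged patients whom the Discussion says the design brings in.

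The second problem is independent of the first. Passing the counselling and message criteria is decided after randomisation and can be failed only in the intervention arm. If patients who complete most of their calls would have walked more anyway, the retained intervention patients differ from the controls before any treatment effect is counted. The listed adjustments (baseline steps, condition, sex and any baseline measure found to differ) remove this only so far as they capture that tendency.

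**Working it through.** **1. The syncing criterion against the diary pathway (no arithmetic)**

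| Step | Patient without a smartphone |
|---|---|
| Eligible? | Yes (Patient eligibility) |
| Asked to do what? | Keep a paper step diary (Phone contact section) |
| Offered what in the intervention arm? | Adapted messages (mHealth intervention section) |
| Counted as per-protocol? | No, because the tracker is not synced monthly (Statistical analysis) |

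Syncing through someone else's phone does not resolve this. The section on the second baseline visit suggests relatives or friends only for the initial set-up.

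**2. The plan's own sample size**

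Inputs from the Sample size section: difference 1000, SD 3000, two-sided alpha 0.05, power 80%, attrition about 15%. The two-sample t-test calculation gives 142.25, rounded up to 143 per arm, as stated. Then 286 / 0.85 = 336.5, or 337, against 340 planned. With 340 × 0.85 = 289 analysed, power is 0.81. These figures are sound and are used below.

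**3. Shift from filtering one arm, with no true effect**

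Let *p* be the share of the intervention arm passing the counselling and message criteria, and ρ the correlation between the tendency to adhere and 12-month steps left after adjustment. The documents give neither, so both are assumed ranges. Taking the tendency as normal and passing as its top fraction *p*:

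shift = ρ × SD × φ(z₁₋ₚ) / p

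- p = 0.8: φ(z)/p = 0.350, so 3000 × 0.350 × ρ = 0, 105, 210, 315 steps/day for ρ = 0, 0.1, 0.2, 0.3.
- p = 0.6: φ(z)/p = 0.644, so 0, 193, 386, 580 steps/day for the same ρ.

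Two considerations lower these figures:

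- *Baseline adjustment.* If 3000 is the SD before adjustment and baseline correlates 0.5–0.7 with 12-month steps (assumed), the residual SD is 3000 × √(1 − r²). The top value becomes 580 × 0.866 = 502 or 580 × 0.714 = 414.
- *Syncing filter in both arms.* If 80% sync, and the tendency to sync correlates 0.5–0.7 with the tendency to adhere (both assumed), simulation at SD 3000 and ρ = 0.3 gives about 454 down to 386 for p = 0.6, and 219 down to 163 for p = 0.8.

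**4. What the shift would do to a nominal test**

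Suppose 10% of each arm is lost to the syncing criterion (assumed). Controls number 144.5 × 0.9 = 130, and intervention patients 130 × p. The standard error is 3000 × √(1/130 + 1/104) = 395 for p = 0.8 and 3000 × √(1/130 + 1/78) = 430 for p = 0.6. Using the shifts before the two reductions above, the chance of a nominally significant per-protocol result under no true effect, for ρ from 0.1 to 0.3, is 5.8–12.6% (p = 0.8) and 7.3–27.1% (p = 0.6), against 5%.

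**5. Precision**

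Starting from 289 analysable patients, per-protocol power for 1000 steps/day is 0.72 if 10% fail the syncing criterion and 80% of the intervention arm pass the rest. It is 0.54 if 30% fail and 60% pass.

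**The case against.** Several points on the other side stand:

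- Smartphone ownership precedes randomisation and the syncing criterion applies to both arms. A reader might infer that dropping these patients biases the contrast. It mainly changes whom the result describes.
- Limiting a supplementary analysis to patients who sync is a coherent choice, since the article says the full intervention needs a smartphone. That would justify a differently labelled set, but not calling it per-protocol when the protocol itself assigns the diary.
- A reader might infer that the bias favours the intervention and is as large as the roughly 400–550 steps/day seen in the trials cited in the Background. The documents support neither. The criterion "c) receiving text messages for the entire study duration (intervention arm only") concerns largely automated messages and need not select on motivation. Counselling may also keep less motivated intervention patients syncing, while controls who sync do so unprompted by a counsellor, which would push the other way. The likeness to other trials' effects follows from assumed inputs.
- A reader might infer that arm-specific criteria unblind the analyst. Nothing says that the blinded analyst derives the flag, and data access is constrained by role.
- A reader might infer that the per-protocol result could override intention-to-treat. The article does not say so, and ranking the two may be left to the analysis plan, which is not shown.

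None of this touches the two faults in the stated rule: its mismatch with the diary pathway and its one-arm filtering.

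**Conclusion.** The point holds as a fault in the definition of the per-protocol set. The syncing criterion conflicts with the pathway the protocol gives to patients without a smartphone or unable to sync. That conflict is certain from the text, and its consequence is mainly a narrower population. How many patients it affects is not given.

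The one-arm criteria leave the contrast unprotected by randomisation. A bias is possible, of unknown sign. The 0 to about 580 steps/day is an illustration that assumes better adherers walk more, SD 3000, a 60–80% pass rate and a residual correlation of 0–0.3. It is zero if adherence is unrelated to residual steps. Because the intention-to-treat analysis keeps every randomised patient, the trial's main estimate is not in question. The change should be made, but the trial does not stand or fall by it.

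**What to change.** 1. Apply the syncing criterion only to patients able to sync. For patients assigned to the diary, waive it, or accept diary-keeping where diaries are actually collected. The article does not say that they are, and the Process evaluation section does not list them among its data sources. Record the diary assignment in both arms, because inability to sync despite support becomes known only after allocation.
2. Report the per-protocol result as supportive of intention-to-treat. Add, or use in its place, either a complier-average causal effect with randomisation as the instrument or an inverse-probability-weighted analysis that models who adheres. The number of calls and the messages sent are already available from the counsellors' notes and HealthReact.

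The cost is wording plus one model, a wider interval and assumptions that must be stated. The complier estimate assumes no effect below the adherence threshold, yet four calls and 11 months of messages is not zero treatment. Dividing by the share passing multiplies the intention-to-treat effect by 1/0.8 = 1.25 to 1/0.6 = 1.67, which overstates the effect if partial treatment works. A lower threshold, or a dose measure such as number of calls or months of messages, should be run as a sensitivity analysis. Weighting instead assumes that the measured variables explain adherence.

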### Process evaluation

The process evaluation will be conducted alongside the effectiveness evaluation to understand how the intervention is delivered and received and how this may affect the variation in outcomes. The framework for the process evaluation will be guided by the Medical Research Council (MRC) guidance for process evaluations of complex interventions [93] and will include both qualitative and quantitative components. In line with the MRC guidelines, we will investigate intervention aspects such as implementation (which comprises implementation process, reach, fidelity, dose and adaptations), mechanisms of impact, context, and the relations between these. We will use various data sources (forms filled by the GPs, notes taken by the counsellors, data from REDCap electronic data capture tools, data from Fitbit and HealthReact) to devise measures such as the percentage of patients who declined participation and reasons for their non-participation, number and duration of the phone counselling sessions, frequency of syncing the Fitbit monitor, number of just-in-time prompts, whether a patient received full or adapted mHealth intervention, etc. Selected measures will be used as predictor variables in linear models to estimate their effect on PA outcomes. In addition, we will conduct qualitative semi-structured interviews to explore the barriers and facilitators to the acceptability of and adherence to the intervention and to identify the factors that supported the improvement in physical behaviours of the patients from the intervention arm (Additional file 4).

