#### mHealth intervention

The mHealth intervention has been developed with the involvement of (pre)diabetes patients according to the mHealth development and evaluation framework [70, 71]. This framework consists of four sequential phases: (a) conceptualisation, (b) formative research based on focus groups with the target population, (c) pre-testing of specific messages, and (d) piloting [71]. The intervention development and the messages' content and triggering rules will be described in a separate paper. In brief, the patients receive six types of text messages involving various behaviour change techniques (Table 2) [72]. (1) Just-in-time prompts to increase walking pace are triggered when the patient is actually walking (5 consecutive minutes with steps per minute in the range from 60 to 100). (2) Just-in-time prompts to interrupt sitting are sent when the patient sits for more than 30 min. (3) Interim reviews of patients’ weekly step goals are triggered on Friday evening, highlighting the potential discrepancy between the goal and actual step count so that the patients have a chance to catch up over the weekend. (4) At the end of the week, on Sunday evening, patients receive feedback on their weekly performance and encouragement for the upcoming week. (5) Reminders of the action plans are adapted to specific plans of each patient as set during the phone counselling session (e.g., patients are reminded to go for a short walk after lunch or to walk their dog on a pre-specified day and time). (6) Finally, short educational messages are sent occasionally to highlight the importance of PA in (pre)diabetes management.

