The mHealth intervention is enabled by the HealthReact system developed at the University of Hradec Kralove [73]. HealthReact consists of a server-side application connected to the Fitbit server and thus can trigger sending out just-in-time text messages based on the data recorded by the Fitbit tracker (Fig. 2). Researchers can choose from a wide variety of just-in-time triggers to suit study objectives and adapt the triggers to the specific needs of individual patients. The HealthReact system enables the setting of certain parameters to regulate the number of text messages sent (e.g., total number of just-in-time prompts per day, the minimum time between two prompts, the time window when prompts are triggered, the probability that a triggered text message is actually sent out). These parameters are tuned so that the total number of text messages per week ranges between 4 and 6.

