In addition to pre-/post-intervention outcomes, the Fitbit data will be used to explore short-term changes in behaviour proximal to the triggered text messages using a micro-randomisation design [88]. Briefly, HealthReact enables setting a probability that a triggered text message is actually sent out, thus enabling micro-randomisation. We will set the probability of sending out each triggered text message to 50% (i.e., only every other text message that is triggered will be actually sent out). Thus, we will be able to compare physical (in)activity, as recorded by Fitbit after the trigger, between text messages that were actually sent and those that were not. For different types of text messages, we will evaluate various time periods after the trigger: for just-in-time prompts to increase walking pace or interrupt sitting, we will evaluate periods ranging from 5 to 15 min; for the action plan reminders, we will evaluate periods ranging from one hour to one day; for the review of the weekly goal and the feedback on weekly performance, we will evaluate periods ranging from one day to one week. In addition, we will explore the moderating effect of the context (e.g., time of the day, day of the week, weather, actual patient performance) on the impact of individual text messages.

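### Counts of just-in-time prompts cannot support an effect estimate in the process evaluation, because the patient's own walking or sitting (and access to syncing) determines how many are sent

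*Protocol article*

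**What the plan says.** Under Methods, Process evaluation, the protocol article lists candidate measures that include "frequency of syncing the Fitbit monitor, number of just-in-time prompts, whether a patient received full or adapted mHealth intervention, etc", and then states: "Selected measures will be used as predictor variables in linear models to estimate their effect on PA outcomes". It does not call these models descriptive and does not connect them to the message-level randomisation.

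The mHealth intervention section defines the two just-in-time triggers. For the first, "Just-in-time prompts to increase walking pace are triggered when the patient is actually walking", defined as five consecutive minutes at 60 to 100 steps per minute. For the second, "Just-in-time prompts to interrupt sitting are sent when the patient sits for more than 30 min". On overall volume it says "These parameters are tuned so that the total number of text messages per week ranges between 4 and 6", counting all six message types.

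The same section and the Discussion explain that patients who cannot sync reliably, or who have no smartphone, receive an adapted version in which some or all just-in-time prompts are replaced.

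Outcome measures describes a micro-randomisation: "We will set the probability of sending out each triggered text message to 50" per cent. Fitbit activity after sent and unsent triggers is then compared over windows from 5 minutes to one week, depending on message type. The Conclusions say the process evaluation should help improve the next version of the intervention.

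**The concern.** The predictor is partly produced by the outcome behaviour. A patient who spends more time walking in the trigger band generates more walking prompts, and a patient who sits for long spells generates more sitting prompts, whether or not any prompt changes behaviour. Regressing physical activity on the number delivered mixes any effect of the prompts with the behaviour that set them off.

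Patients who cannot sync receive few or no just-in-time prompts. The Discussion links the inclusion of patients without a smartphone to older age and lower socioeconomic status, so the count also carries ordinary confounding by access.

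Number of calls, syncing frequency and full-versus-adapted delivery are a separate problem. Walking does not trigger them, but they are open to confounding by adherence or access.

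At stake is how the process results are used. A spurious dose-response could suggest sending more of one prompt type or dropping the other in the next version.

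**Working it through.** The plan gives no figure for this analysis, so there is none to reproduce. The question is whether a model with a true prompt effect of zero returns a zero slope.

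**Inputs from the documents.** 340 patients allocated 1:1 give 340 / 2 = 170 in the intervention arm. Sending probability is 0.5. The SD of 3000 steps/day comes from Sample size.

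**Assumed inputs (not in the documents).** Mean 7000 steps/day at baseline. Habitual activity during the trial, A, equals baseline plus a change with SD 1500. Twelve-month steps equal A plus independent variation with SD 1500. There are 6 triggers per week at A = 7000 and 52 weeks. Walking triggers are proportional to A: 6 × A / 7000. Sitting triggers fall with A: 6 × exp(-(A - 7000) / 7000). Prompts change nothing.

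**Walking prompts, by hand.**
- Expected prompts sent per week = 0.5 × 6 × A / 7000 = 3A / 7000. Sending half the triggers halves the count but leaves it proportional to A.
- Given baseline, the variance of A is 1500² = 2.25 million. The variance in prompts per week due to activity is (3/7000)² × 2.25 million = 0.413.
- Chance variation in the 52-week mean is about 3 / 52 = 0.058.
- Baseline-adjusted slope = (7000/3) × 0.413 / (0.413 + 0.058) ≈ 2050 steps/day per weekly prompt, although the true effect is zero.

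Baseline adjustment fails because activity drifts from baseline during follow-up, and that drift drives both the triggers and the 12-month outcome.

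**Simulation with the same inputs (500 replicates).**

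| Predictor | Unadjusted slope | p<0.05 | Baseline-adjusted slope | p<0.05 |
|---|---|---|---|---|
| Walking prompts | +2288 | 100% | +2059 | 100% |
| Sitting prompts | -2031 | 100% | -1476 | 100% |
| Both, pooled | -1277 | 38% | -343 | 13% |

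The hand calculation and the simulation agree for walking prompts. Capping prompts at 2 or 1 per week did not remove the bias for a single type: adjusted slopes were +3592 and +6036 for walking, and -6945 and -14010 for sitting, all with p<0.05 in 100% of runs.

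**Why sign and size are not fixed.**
- *Pooling.* The two types bias in opposite directions, so a combined count takes its sign from the mix.
- *Pace band.* Under the second baseline visit, the advice equates 3000 brisk steps with about 30 minutes, which is 3000 / 30 = 100 steps per minute, the upper edge of the trigger band. As an illustration, ten minutes at 80 per minute gives 800 steps inside the band, and ten minutes at 110 gives 1100 steps outside it. Steps rise and triggers fall. Assuming that gained steps are brisk and displace some slow walking (SDs 2600, 1500 and 1000 for baseline, change and measurement; 2 to 6 triggers per week; 300 replicates), the adjusted slope for walking prompts was about -310 to -1060, with p<0.05 in 15 to 32% of runs.
- *Frequent triggers under a cap.* With triggers proportional to steps, those same SDs, a cap of 2 per week and 70 triggers per week, p<0.05 occurred in 42% of runs rather than all.

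**An exposure that is free of this bias.** Take prompts sent minus 0.5 × eligible triggers. Given the triggers, its weekly variance is 0.25 × 6 = 1.5, and over 52 weeks 1.5 / 52 = 0.029, an SD of 0.17 prompts per week. The residual SD of 12-month steps given baseline is √(1500² + 1500²) = 2121. The standard error of the slope is about 2121 / (0.17 × √170) ≈ 960, so the 95% half-width is about 1.96 × 960 ≈ 1880 steps/day per weekly prompt. That is nearly twice the 1000 steps/day on which the trial is sized.

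**The case against.** The strongest reply is that the article commits to little. It speaks only of selected measures, names no covariates, and condenses a fuller protocol. The prompt count may never enter a model. This stands, and it limits the point to the stated purpose of the models: the count is named, nothing excludes it, and the sentence claims an effect.

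A second reply is that the trial already has the right tool. Outcome measures plans the randomised comparison of sent and unsent triggers, with contextual moderators. This also stands, so the trial does not lack a valid source of causal evidence on prompts. But that comparison covers windows of up to one week and does not repair a separate between-patient model.

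A third reply is that researchers partly set the dose, through the weekly total of 4 to 6 messages and the tuning of triggers for individual patients. This weakens the link between activity and count, but it does not break the link for each prompt type. It also leaves more of the variation to syncing and smartphone access.

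A reader might infer that the model must show a falsely favourable dose-response. The documents do not support that. Walking triggers only one of the two types, the pace band leaves out walking above 100 steps per minute, and no trigger rate is given.

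**Conclusion.** The point holds in a limited form. If the prompt count is used as a predictor, its coefficient is not an effect of prompts. It reflects the patient's own walking and sitting, plus access to syncing, and neither baseline adjustment nor 50% sending removes this.

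The figures above rest on assumed trigger rates and activity distributions. They show that the bias can exceed 1000 steps/day per weekly prompt for a single type, that it can largely cancel when types are pooled, and that its sign can reverse. They do not predict what this trial would report.

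Severity is minor. A reader might infer damage to the trial's main result, but the primary comparison is between randomised arms and uses no prompt count. The confounding of call number, syncing and adapted delivery is a separate weakness, to be handled by wording rather than counted as reverse causation.

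**What to change.** In Process evaluation:

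1. Do not use prompt counts to estimate an effect. Replace the effect wording with association for all models on process measures, including calls, syncing and full-versus-adapted delivery.
2. Report walking and sitting prompts separately.
3. State that causal conclusions about prompts come from the sent-versus-unsent contrast under Outcome measures.
4. If a longer-term dose analysis is wanted, use prompts sent minus 0.5 × eligible triggers as the exposure, counting only triggers for which sending was actually randomised, and say in advance that it will be imprecise.

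The change is to wording and can be made before analysis. Item 4 needs a record of eligible triggers, sent and unsent; the planned micro-randomised comparison needs the same record. The downside is that the trial cannot claim a precise 12-month dose-response for prompts.
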